#### Statistical analysis

2.6.2

All statistical analyses will be performed using R software (version 4. X. X; R Foundation for Statistical Computing, Vienna, Austria). All tests will be two-tailed, with statistical significance defined as *p* < 0.05. Continuous variables will be summarized as mean ± standard deviation or median with Interquartile Range (IQR), depending on the data distribution. Categorical variables will be presented as frequencies and percentages.

For the primary outcome, changes in NRS scores will be analyzed according to the data distribution. Between-group comparisons will be performed using an independent *t*-test if the normality assumption is satisfied; otherwise, the Wilcoxon rank-sum test will be used. Within-group changes will be assessed using a paired *t*-test or the Wilcoxon signed-rank test, depending on whether the data meet normality assumptions.

For the secondary outcomes, changes in lumbar ROM from baseline will be analyzed using the same statistical methods applied to the primary outcome. Between-group comparisons will be conducted using an independent *t*-test or the Wilcoxon rank-sum test, while within-group comparisons will be analyzed using a paired *t*-test or the Wilcoxon signed-rank test, depending on data normality.

The ODI will be categorized into predefined functional disability levels, and differences in distribution between groups will be analyzed using the Chi-square test or Fisher’s exact test, as appropriate.

PRPPR will be assessed immediately after treatment and again at 24–36 h post-intervention. Between-group comparisons will be conducted using an independent *t*-test or the Wilcoxon rank-sum test, while within-group comparisons will be analyzed using a paired *t*-test or the Wilcoxon signed-rank test, depending on the data characteristics.

In addition, procedural characteristics and usability-related variables associated with needle length—including deep-layer reach success rate, number of insertions, procedure time, and operator usability score—will be summarized using descriptive statistics. When appropriate, exploratory between-group comparisons will be conducted using the Mann–Whitney U test or the Chi-square test. These analyses will serve as supportive reference analyses and will not directly influence the interpretation of the primary clinical outcomes.

If significant baseline differences are identified between the two groups and these variables are considered potentially related to the outcome measures, they will be treated as possible confounding factors. In such cases, subgroup analyses or multivariate analyses (e.g., ANCOVA or multiple regression models) will be conducted. Adjusted effect sizes with corresponding 95% confidence intervals will be reported to improve the interpretability and accuracy of the findings.

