*If the subject is deemed eligible after screening, the first intervention will be performed immediately after obtaining informed consent. ^†^A telephone-based follow-up will be conducted within 1 day (24–36 h) after Visit 1. ^‡^D indicates “Day.” ^a^Demographic survey: information on gender, age, year of birth, height, weight, and other baseline characteristics will be collected. ^b^Medical history: includes previous history of low back pain(LBP), hypertension, diabetes, osteoarthritis, sleep disorders, psychiatric history, current medications, smoking history, and alcohol consumption. ^c^ODI (Oswestry disability index): the ODI is a validated questionnaire assessing functional disability related to LBP. It consists of 10 items covering pain intensity and daily activities, and yields a score ranging from 0 to 100%, with higher scores indicating greater disability. In this study, ODI is administered only at baseline to evaluate initial functional status. ^d^NRS (numeric rating scale): pain intensity for LBP will be assessed on a 0–10 scale, where higher scores indicate more severe pain. ^e^PRPPR (patient-reported percentage pain reduction): subjects will be asked to report the perceived percentage of pain reduction compared with pre-intervention status, on a 0–100% scale, both immediately after treatment and at Day 1 follow-up. ^f^ROM (range of motion): lumbar ROM—including flexion, extension, lateral flexion, and rotation—will be assessed to evaluate functional changes. ^g^Adverse events: adverse events or unexpected symptoms occurring immediately after the procedure or during follow-up will be assessed and recorded.

The study protocol has been submitted for Institutional Review Board (IRB) approval. Ethical approval will be obtained prior to the initiation of participant enrollment. No participants have been recruited or exposed to the intervention at the time of manuscript submission.

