#### Primary outcome

2.5.1

The primary outcome of this study is the change in Numeric Rating Scale (NRS) scores for LBP immediately following ultrasound-guided pharmacopuncture.

The NRS score recorded immediately before the procedure will serve as the baseline, and a second NRS assessment will be conducted immediately after the intervention (QPI-guided PDRN pharmacopuncture). The difference between the baseline and post-procedure scores will be calculated to determine the extent of symptom improvement. A between-group comparison of NRS changes (SNG versus LNG) will be used to evaluate whether needle length influences the magnitude of acute pain reduction.

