#### Sample size calculation

2.6.1

Since no prior study has been conducted under conditions identical to the present trial, the effect size for this study was estimated based on comparable interventions and studies reporting changes in NRS or VAS as primary outcomes. In a double-blind randomized controlled trial evaluating pharmacopuncture in patients with chronic LBP, the mean reduction in pain after 3 weeks was 2.74 points in the treatment group and 1.76 points in the control group, yielding an estimated between-group difference of approximately 1.0 point and a Cohen’s d of approximately 0.56 (23). Similarly, a systematic review of acupuncture for acute LBP reported a mean difference of −1.75 points on the VAS compared with controls (95% CI: −2.39 to −1.12) (24), indicating a meaningful short-term analgesic benefit. Additionally, a single-arm study conducted in Japan evaluating ultrasound-guided hydrodissection demonstrated a reduction of more than 4 points on the VAS immediately after the procedure (25), suggesting that ultrasound-guided interventions may provide rapid short-term pain relief.

Additionally, although the Minimum Clinically Important Change (MCIC) for acute LBP has been reported to be approximately 3.5 points on the NRS scale (26), such thresholds primarily apply to single-arm studies evaluating absolute symptom improvement. In comparative trial designs, such as the present study, the full magnitude of the MCIC is not required to determine a meaningful treatment difference. Instead, between-group differences of approximately 1 point—similar to those reported in previous randomized controlled trials—may still represent a clinically relevant effect when assessing comparative therapeutic outcomes.

Based on the literature reviewed, the effect size for this study was set at Cohen’s d = 0.56. Using a two-sample *t*-test with a significance level of 0.05 and a statistical power of 80%, the minimum required sample size was calculated to be 104 participants (52 per group). Allowing for an anticipated dropout rate of approximately 10%, the final target sample size was set at 120 participants, with 60 allocated to the short-needle group and 60 to the long-needle group.

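### The primary test is chosen from the outcome data and baseline NRS is adjusted for only after a significance test; one prespecified baseline-adjusted mean-difference model should replace both rules.

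*Protocol article*

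**What the plan says.** Section 2.5.1 defines the primary outcome by subtraction: "The difference between the baseline and post-procedure scores will be calculated to determine the extent of symptom improvement". The groups are then compared on that change: "A between-group comparison of NRS changes (SNG versus LNG) will be used to evaluate whether needle length influences the magnitude of acute pain reduction".

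Section 2.6.2 sets the test: "For the primary outcome, changes in NRS scores will be analyzed according to the data distribution". The independent t-test applies only conditionally, and "otherwise, the Wilcoxon rank-sum test will be used". The article does not name the normality check, its threshold, or whether it applies to each arm or to residuals.

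The last paragraph of 2.6.2 makes adjustment conditional: "If significant baseline differences are identified between the two groups and these variables are considered potentially related to the outcome measures". Only then do subgroup analyses, ANCOVA or multiple regression follow, with adjusted effects and 95% confidence intervals.

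In 2.6.1, "the effect size for this study was set at Cohen’s d = 0.56". This comes from a cited trial with mean reductions of 2.74 and 1.76 points, and the calculation is for a two-sample t-test at 5% significance and 80% power. Section 2.1 states that each site contributes cases for one needle type only, without randomisation.

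**The concern.** The study is justified and sized in mean NRS points. If the normality check fails, the primary comparison becomes a rank test. That test does not estimate a mean difference, and the article names no estimate to go with it. The reader could be left with a p-value that does not speak to the 1-point difference argued for in 2.6.1. Which of the two analyses is primary is not known until the outcome data are seen.

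The second issue is baseline pain. A change score uses the baseline with its coefficient fixed at 1. This is less efficient than estimating the coefficient, and it leaves the comparison exposed when the groups start from different pain levels. That matters here because needle length is set by clinic and 2.3.2 requires no minimum NRS. The safeguard in 2.6.2 depends on a baseline significance test, which responds to sample size and chance as well as to the amount of confounding.

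**Working it through.** **1. The plan's own figure.** Inputs from 2.6.1 and 2.6.2: d = 0.56, two-sided 5%, 80% power. The exact two-sample t-test solution is 51.03, so 52 per group and 104 in all, as stated. Power is 80.7% at 52 per group and 86.0% at 60. The implied SD of the change is (2.74 − 1.76)/0.56 = 0.98/0.56 = 1.75.

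**2. How often would the test switch?** The Table 1 footnote says "pain intensity for LBP will be assessed on a 0–10 scale, where higher scores indicate more severe pain"; whole-number scoring is an assumption. Simulations used 60 per group and a 5% check, with a switch if either arm rejects unless stated otherwise. The bounded version also assumes baseline mean 6 and SD 1.5, limited to 3–10, with a mean fall of 2 points in the reference group.

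| Check, change SD 1.75 | Switches to Wilcoxon |
|---|---|
| Lilliefors, by arm | 99.9% |
| Shapiro-Wilk, by arm | 91% (94–96% with the 0–10 bounds) |
| Shapiro-Wilk on residuals | 63–70% |
| Kolmogorov-Smirnov, estimated parameters | 31% |
| D'Agostino | 11% |
| Jarque-Bera | 8% |

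For Shapiro-Wilk by arm without bounds, the rate falls from 99.5% at SD 1.5 to 72% at SD 2.0 and 42% at SD 2.5.

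**3. What does switching cost?** At SD 1.75, difference 0.98 and 60 per group, using Shapiro-Wilk by arm:

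| Data | t-test | Wilcoxon | Two-stage rule |
|---|---|---|---|
| Rounded normal | 85.9% | 83.7% | 83.9% |
| Bounded 0–10 | 81.9% | 81.0% | 81.0% |

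Type I error of the two-stage rule was 4.7–5.7% across all scenarios.

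**4. Would the baseline trigger catch an imbalance?** Assume baseline SD 1.7, 60 per group and a true gap of 0.5 points. The standard error is 1.7 × √(2/60) = 0.310, and 0.5/0.310 = 1.61. The chance of p < 0.05 is about Φ(1.61 − 1.96) = 36%, so about 64% of such studies would go unadjusted.

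With equal pre and post SDs, expected change rises by (1 − ρ) per baseline point. For ρ = 0.4, 0.5 and 0.6 a 0.5-point gap shifts the change comparison by 0.30, 0.25 and 0.20 points, or about 20–31% of 0.98. This applies where the gap regresses to the mean; it need not apply to a stable difference between clinics.

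**5. Precision from using baseline NRS as a covariate.** With equal SDs, the change-score variance is 2σ²(1 − ρ) and the ANCOVA residual variance is σ²(1 − ρ²). Their ratio is (1 + ρ)/2. The documents give no ρ, so a range is shown, with d = 0.56 held on the change score.

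| ρ (assumed) | Ratio | Power at 52 per group |
|---|---|---|
| Planned change score | 1 | 80.7% |
| 0.4 | 0.70 | 92.2% |
| 0.5 | 0.75 | 90.4% |
| 0.6 | 0.80 | 88.5% |

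**6. Can site be added?** With four sites and one needle type per site, a model with an intercept, group and three site indicators has 5 columns but rank 4. The needle effect is not identifiable.

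**The case against.** Much can be said for the plan. A change score does use the baseline, so a reader who infers that baseline information is thrown away goes too far. Nor is adjustment absent: the last paragraph of 2.6.2 allows ANCOVA or regression with 95% confidence intervals, and group summaries by mean and SD or median and IQR are planned in either branch. The planned test meets its 80% target. All of this stands. What it leaves open is that adjustment is reached only through a significance trigger that misses most moderate gaps.

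A reader might also infer that the t-test will almost never be run. The article does not support that: it names no check and does not say that a formal test will be used, and the simulated rates span 8% to 99.9%. Nor does switching invalidate the inference, as step 3 shows.

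The strongest objection is that ANCOVA is not plainly better in non-randomised groups. If clinics differ stably in baseline pain, ANCOVA can be biased where the change score is not; if the gap regresses to the mean, the reverse holds. This stands, and it is why both estimates should be reported.

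**Conclusion.** The point holds in a limited form. The protocol fixes a rule under which the outcome data select the primary test, while the sample size covers only the t-test branch and the rank branch has no stated effect estimate. A switch is likely under some common checks and unlikely under others. The consequence is a change in what is estimated, not a material loss of power or of error control.

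The baseline-significance trigger is a weak safeguard: about 36% detection of a true 0.5-point gap, assuming SD 1.7 and 60 per group. The gain in power from 81% to 89–92% assumes a pre-post correlation of 0.4–0.6, equal SDs, independent patients and no systematic baseline difference. Site-based allocation means that the last two cannot be taken for granted. It would be wrong to infer that the adjusted model cures the design: needle length stays confounded with site under any of these analyses.

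**What to change.** In 2.6.2, prespecify one primary model: linear regression of post-procedure NRS on needle group and baseline NRS, plus confounders named in advance from data already collected (for example age, sex, height and weight, previous low back pain and baseline ODI). Report the adjusted mean difference and its 95% CI whatever the distribution.

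Delete the normality pre-test and the baseline-significance trigger. Keep the unadjusted change-score t-test and the Wilcoxon test as sensitivity analyses. Report the change-score mean difference with its CI next to the adjusted one, and say that disagreement between them reflects baseline differences between non-randomised groups. Do not enter site as a fixed effect, and state that the model does not separate needle length from site.

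The cost is wording only: no new data and no change to the target of 120. The article reports that nobody had been recruited at submission, so the change is best made before enrolment.

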##### Functional disability assessed using the ODI

2.5.2.2

The ODI is a standardized, self-reported questionnaire designed to assess functional disability related to LBP. It comprises 10 items, and the final score is expressed as a percentage ranging from 0 to 100%, with higher scores indicating greater disability. In this study, the baseline ODI score will be used as a descriptive measure of the participants’ functional limitations (19).

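### Baseline ODI, a 0–100% score, is compared between groups as unordered disability levels, which costs about 23–31 points of power against a moderate imbalance under stated assumptions; a minor, free improvement

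*Protocol article*

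**What the plan says.** The protocol article lists ODI under secondary outcomes (2.5.2.2). It describes a 10-item questionnaire for which "the final score is expressed as a percentage ranging from 0 to 100%, with higher scores indicating greater disability". The footnote to Table 1 says "ODI is administered only at baseline to evaluate initial functional status", and 2.5.2.2 says "the baseline ODI score will be used as a descriptive measure of the participants’ functional limitations".

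Section 2.6.2 then fixes the analysis: "The ODI will be categorized into predefined functional disability levels, and differences in distribution between groups will be analyzed using the Chi-square test", with Fisher's exact test as the alternative. The cut points and the number of levels are not given. NRS change, ROM change and PRPPR are each compared on their full scale by t-test or Wilcoxon rank-sum test.

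The last paragraph of 2.6.2 makes adjustment conditional: "If significant baseline differences are identified between the two groups and these variables are considered potentially related to the outcome measures", those variables are treated as possible confounders and subgroup or multivariable analyses follow. The test that identifies such differences is not named.

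**The concern.** Two kinds of information are lost. Patients within one level are treated as identical, although their scores may differ by many points. The levels are then compared by tests that would give the same p-value if the levels were shuffled, so several degrees of freedom are spent on what would normally be a shift in one direction. No reason is given for treating ODI differently from the other scales.

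The comparison has some importance here because the groups are formed by clinic, two clinics per needle length, without randomisation. The article itself lists selection bias from this as a limitation. ODI is the only disability questionnaire taken at baseline, and this is the only ODI comparison the article states. If the same test also decides whether ODI counts as a baseline difference, a real imbalance in disability is more likely to be reported as absent, and the NRS comparison is more likely to stay unadjusted for it.

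**Working it through.** **Inputs from the document.** Two-sided 5% level (2.6.2); d = 0.56 and 52 per group as the minimum, 60 per group as the target (2.6.1); ODI range 0–100% (2.5.2.2); pain reductions of 2.74 and 1.76 points in the trial used for planning (2.6.1).

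**Inputs assumed, because the document gives none.** ODI cut at 20/40/60/80; mean 30–50 and SD 12–20; scores in 2-point steps, normal or right-skewed; independent patients; a true imbalance of 0.2–1.0 SD; correlation of 0.3 between ODI and NRS change.

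**The plan's own figure.** Section 2.6.1 says "the effect size for this study was set at Cohen’s d = 0.56". At 80% power and two-sided 5%, the exact two-sample t-test needs 51.03 per group, rounded up to 52, so 104 in total. With 10% dropout, 104 / 0.9 = 115.6, so 116; the target of 120 exceeds it. The figure reproduces. It concerns NRS. The document states no power for the ODI comparison, so 0.56 SD serves below only as a yardstick.

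**Power to detect an ODI imbalance.** Simulated trials, 60 per group, normal scores, five levels, ranges over the assumed means and SDs:

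| True imbalance | Loss, chi-square on levels versus t-test on score |
|---|---|
| 0.2 SD | about 9 points |
| 0.3 SD | 17–20 points |
| 0.4 SD | 23–30 points |
| 0.5 SD | 25–32 points |
| 0.56 SD | 24–31 points |
| 0.7 SD | 14–18 points |
| 0.8 SD | 7–8 points (typical) |
| 1.0 SD | about 1 point |

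In levels of power, the base case (mean 40, SD 15) gives 86% against 61% at 0.56 SD and 58% against about 32% at 0.4 SD. With 52 per group, the 0.56 SD figures are 80% against 53%.

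**Sensitivity at 0.4–0.56 SD.**
- Five levels, skewed scores included: median loss 25–27 points, single scenarios about 10 to 34.
- Four levels: median about 21–23. Three or two levels: median about 18–22. Single scenarios spread more widely with these cuts, from about 1 point (three levels) to 48 points (two levels).
- Five levels treated as ordered: the loss drops to about 3–9 points at 0.5–0.56 SD. Most of the loss therefore comes from ignoring order.

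**Possible effect on the NRS result.** Suppose this test is the trigger and adjustment removes the bias whenever it is significant. The SD of NRS change implied by the planning figures is (2.74 − 1.76) / 0.56 = 0.98 / 0.56 = 1.75.
- An imbalance of 0.56 SD left wholly unadjusted gives a bias of 0.3 × 0.56 × 1.75 = 0.29 points.
- Trials in which chi-square misses it have smaller realised imbalances, on average 0.40–0.42 SD: 0.3 × 0.41 × 1.75 = 0.22 points.
- Averaged over all trials, with chi-square missing about 39% of the time: 0.39 × 0.22 = 0.08–0.09 points. With a t-test on the score, the same average is about 0.02.
- The difference, which is the part due to categorising, is about 0.06–0.07 points, or 6–7% of the planned 1-point effect. At 0.4 SD the averages are about 0.11 and 0.05, a difference of about 0.06.

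**The case against.** ODI carries no treatment inference. It is measured once, before the injection, and is called descriptive. No hypothesis or sample size rests on it, and the general rule in 2.6.2 would allow it to be summarised as a mean or median as well. The contrast with NRS, ROM and PRPPR is therefore not quite like with like. This stands, and it is why the point is minor.

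Three stronger readings are tempting, and the document does not support them.

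- **A fixed loss of 23–30 points.** That size belongs to a moderate imbalance, near-normal scores and about five levels. It is much smaller for small or large imbalances and varies with the cuts, which are not stated.
- **The ODI test directly controls adjustment of the primary result.** The conditional-adjustment paragraph names no test. It also requires that the variable be considered related to the outcome, and it does not say ODI would enter a model as levels. The link is a plausible inference only. If ODI did enter as five levels, about 8–20% of the confounding bias would remain, so most would still be removed.
- **A bias of about 0.3 NRS points, or 30% of the planned effect.** That applies the full population imbalance as though it were never adjusted for, and assigns all of it to categorising. A t-test on the score also misses imbalances: about 42% of the time at 0.4 SD and 14% at 0.56 SD.

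The dependence of adjustment on a significance test is a separate weakness. A sharper ODI test leaves it in place, whereas adjustment for ODI specified in advance would remove it. None of this makes an unordered test on levels a good choice: even as pure description, a difference with its interval says more about whether the clinics' patients are comparable than a chi-square p-value does.

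**Conclusion.** The point holds as a minor one. The article fixes an analysis of baseline ODI that discards information for no stated reason. Given five 20-point levels, near-normal scores, 60 per group and independent patients, the cost is about 23–31 points of power at imbalances of 0.4 and 0.56 SD, slightly more in between, and under 10 points at 0.2 or 0.8 SD. Independence is itself doubtful with two clinics per group. The direction does not depend on the unstated cuts; the size does.

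The consequence for the primary NRS comparison is indirect and small: about 0.06–0.07 points on average, conditional on this test serving as the adjustment trigger, a true imbalance of 0.4–0.56 SD and a correlation of 0.3. The case for changing the plan is that a better method is available at no cost, not that the primary result is at serious risk.

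**What to change.** Replace the ODI sentence in 2.6.2 with wording such as:

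> Baseline ODI will be summarised by group on its 0–100% scale (mean and SD, or median and IQR), with the between-group difference and its 95% confidence interval. Any comparison will use the full score (t-test or Wilcoxon rank-sum test). Disability levels will be tabulated for description only, without a test. Wherever ODI is used for adjustment, it will enter the model as a continuous covariate.

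This needs no new data, visits or patients, and the table of levels can stay. Section 2.1 says no participants had been recruited at submission, so on that statement the change could precede any data. The change does not touch the significance-based trigger for adjustment, which should be considered separately.

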**Methods:**

This prospective, multicenter, comparative observational study includes adults aged 20–65 years presenting with acute LBP within 7 days of onset. Participants undergo a single session of ultrasound-guided Polydeoxyribonucleotide (PDRN) pharmacopuncture targeting the QPI interfascial plane using either a short needle (26G × 60 mm) or a long needle (25G × 100 mm). Group assignment is based on pre-designated site-level data extraction rather than randomization. The primary outcome is the change in the Numeric Rating Scale (NRS) score immediately after treatment. Secondary outcomes include changes in lumbar range of motion (ROM), patient-reported percentage pain reduction (PRPPR), and procedural usability. Safety is monitored immediately post-procedure and again during a telephone follow-up 24–36 h later. Statistical analyses will compare between-group effects and explore potential associations with procedural characteristics.

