### Study design

2.1

This prospective, multicenter, comparative observational study aims to evaluate whether needle length (Long versus Short) influences procedural usability, deep target achievement rate, clinical effectiveness, and safety during ultrasound-guided pharmacopuncture for acute LBP. The intervention targets the interfascial plane formed by the QL, PM, and IC muscles—referred to as the “QPI space.” The anatomical location and ultrasound appearance of the QPI interfascial space are illustrated in Figure 1. All procedures are performed under real-time ultrasound guidance. Polydeoxyribonucleotide (PDRN) derived from salmon is used as the pharmacological agent, and a magnetic needle–guided tracking system is applied to deliver 1–2 mL of the injectate into the target layer.

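### ODI is measured only before treatment, yet it is listed and tested between groups as a secondary outcome; usability and deep-target reach have no consistent outcome status

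*Protocol article*

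**What the plan says.** **ODI.** Section 2.1 places ODI among the assessments made before the procedure. Table 1 schedules it at baseline only, and note c to that table confirms this: "In this study, ODI is administered only at baseline to evaluate initial functional status". Section 2.5.2.2, headed "Functional disability assessed using the ODI", says that "the baseline ODI score will be used as a descriptive measure of the participants’ functional limitations". That section is nevertheless the second of three entries under Secondary outcomes (2.5.2), between ROM and PRPPR. The text on unblinded assessment in section 2.5.2.3 also counts ODI among the outcome measures. Section 2.6.2, again between ROM and PRPPR, plans a between-group test of it, with a Fisher test as the alternative: "The ODI will be categorized into predefined functional disability levels, and differences in distribution between groups will be analyzed using the Chi-square test".

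**Baseline differences.** The last paragraph of section 2.6.2 makes covariate adjustment (ANCOVA or regression) or subgroup analysis conditional on finding a significant baseline difference in a variable thought to be related to outcome.

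**Procedural measures.** Section 2.1 says the study evaluates whether needle length "influences procedural usability, deep target achievement rate, clinical effectiveness, and safety". The abstract states: "Secondary outcomes include changes in lumbar range of motion (ROM), patient-reported percentage pain reduction (PRPPR), and procedural usability". The end of the Introduction describes reachability, usability and safety as secondary and exploratory in the same phrase. Section 2.5.2 has no entry for reach or usability. Section 2.6.2 summarises both descriptively, allows exploratory tests where appropriate, and treats the results as supportive.

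**The concern.** A variable recorded before the needle is inserted cannot respond to the needle. A between-group test of it compares the patients of two clinics with the patients of the other two. When such a test is filed with the secondary outcomes, a baseline comparison is reported in the place where treatment comparisons belong. The protocol also leaves it unclear whether ODI is there to describe the sample, to check comparability or to act as an endpoint.

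This matters more here than in a randomised trial. Two clinics contribute only short-needle cases and two only long-needle cases (section 2.1), and the Discussion concedes possible selection bias. Initial disability may plausibly differ between the groups. The useful role for ODI is then adjustment, but the plan makes that depend on a significance test.

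The second issue is that the measures closest to the needle-length question have a different rank depending on which section is read. The Discussion puts the target at about 4–6 cm or deeper and says that 50–60 mm needles may give limited access. Whether the tip arrives is therefore central to the comparison, and its standing should be settled before results are seen.

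**Working it through.** **1. The plan's own figure.** With d = 0.56, two-sided alpha 0.05 and 80% power, the normal approximation gives n = 2(1.960 + 0.842)² / 0.56² = 50.1, so 51 per group. The exact t-based solution is 51.03, so 52 per group and 104 in total, as stated (power 80.7%). A 10% dropout allowance gives 104 / 0.9 = 115.6, so 116; the target of 120 rounds this up. The figure reproduces, and nothing below changes it.

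**2. ODI, statement by statement.**
- Timing: before the procedure only (section 2.1; Table 1 and its note c).
- Stated purpose: descriptive (section 2.5.2.2).
- Classification: secondary outcome (position under 2.5.2) and outcome measure (2.5.2.3).
- Analysis: between-group chi-square or Fisher test (section 2.6.2).

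The first two statements are compatible with each other. The last two are not compatible with them. There is no post-treatment ODI, so no change score can be formed and no needle effect on ODI can be estimated.

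**3. What the ODI test can show.** If the clinics' populations have the same ODI distribution, the test rejects about 5% of the time. If they differ, it rejects more often, and what it detects is case mix.

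The protocol gives neither an ODI distribution nor the number of levels, so the following is an illustration on assumed values: five levels, 60 per group, 4 degrees of freedom. The short-needle proportions are taken as (0.10, 0.30, 0.35, 0.20, 0.05). The noncentrality is λ = 60 × Σ[(p₀ − p̄)²/p̄ + (p₁ − p̄)²/p̄], with p̄ the mean of the two proportions at each level.
- Long-needle proportions identical: λ = 0, rejection 5%.
- Long-needle proportions (0.06, 0.24, 0.35, 0.26, 0.09): λ = 2.16, rejection about 18%.
- Long-needle proportions (0.05, 0.20, 0.35, 0.30, 0.10): λ = 4.40, rejection about 35%.

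There is no treatment effect in any of the three. If this test served as the trigger for adjustment, these two assumed imbalances would go unflagged about 82% and 65% of the time (1 − 0.18 and 1 − 0.35). The percentages depend wholly on the assumed distributions and are not estimates for this study.

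**4. Procedural measures, place by place.**
- Usability: an aim in 2.1; secondary in the abstract; secondary and exploratory in the Introduction; no entry in 2.5.2; supportive and exploratory in 2.6.2.
- Deep-target reach: an aim in 2.1; not named in the abstract's secondary list; secondary and exploratory in the Introduction; no entry in 2.5.2; supportive and exploratory in 2.6.2.
- Data: section 2.1 records tip arrival and an operator usability questionnaire, so both are available.

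**The case against.** The strongest defence of the ODI test is that it is a comparability check. In a study allocated by clinic, a significant result may reflect a true difference between clinic populations, and section 2.6.2 uses significant baseline differences to trigger adjustment. Part of this stands: a rejection would not necessarily be a chance finding, and deleting the test without providing for adjustment would leave that rule with no ODI input. But the protocol does not give the test this role. It files ODI as a secondary outcome and places the test between two outcome analyses.

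A reader might infer that an ODI difference would be presented as a needle effect on disability. The documents do not support that. They label ODI as baseline repeatedly and never speak of a change in it. A reader might also infer that cutting the score into levels removes it as a covariate. It does not: the 0–100% score is collected and can still enter a model.

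On the procedural measures, a reader might conclude that reach and usability are unmeasured or have no status at all. They are recorded, summarised and given exploratory comparisons, and the abstract names usability as secondary. Nor do the documents require reach to be secondary: the abstract does not list it, and an aim in section 2.1 does not fix an outcome tier. Consistent exploratory status would be equally acceptable. Keeping supportive analyses from influencing the primary interpretation is no fault either.

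**Conclusion.** The point holds as a matter of classification and analysis choice. ODI is a baseline characteristic that the protocol lists and tests as a secondary outcome, so one of the three entries in section 2.5.2 (ROM, ODI, PRPPR) cannot inform on needle length. This follows from the measurement schedule alone and needs no numerical assumption; the rejection rates above are illustrative only. Usability and deep-target reach lack one consistent status across the abstract, Introduction, section 2.5.2 and section 2.6.2, and neither has an entry in 2.5.2. The weight is moderate: the primary outcome and the sample size are untouched, and the data needed for the correction are already to be collected.

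**What to change.** 1. Move ODI from section 2.5.2 to baseline characteristics, and take it out of the outcome measures named in 2.5.2.3. Remove its between-group test as an outcome analysis and report the baseline difference between groups descriptively.
2. Prespecify the continuous baseline ODI score as a covariate in the adjusted (ANCOVA or regression) analysis of NRS change, so that its use does not depend on a significant baseline difference. State whether this model stands next to the unadjusted t-test or Wilcoxon test or replaces it, and which of them is primary.
3. Give procedural usability and deep-target reach one status, secondary or exploratory, and use it in the abstract, Introduction, 2.5.2 and 2.6.2. Report a between-group difference with 95% CI for each.

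**Cost.** Items 1 and 3 are mainly changes of wording, with an interval added for each procedural measure. Item 2 is a small analytic change: the adjusted model is run in every case, and if it replaces the unadjusted test the primary analysis changes. No extra measurement is needed, and section 2.1 states that nobody had been recruited at submission. Adjusting for ODI deals with that one measured difference only; it does not remove other differences between clinics.
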